### Randomization and blinding

2.2

In this study, the randomization procedure uses a computer-generated sequence of random numbers. Patients will be assigned to the intervention and standard care groups in a 1:1 ratio. This randomization process will take place prior to patient admission. The aim is to ensure that each patient is assigned to the appropriate study group in a predefined order, thus ensuring randomization and fairness of allocation. When patients are admitted to the hospital, they will be assigned a unique code. This code is consistent with the sequence of random numbers and ensures smooth and consecutive enrollment of patients. Once randomization is complete, patients are directed to the appropriate hospital room based on their grouping. Specifically, patients in the intervention group are sent to Ward A, while those in the control group are sent to Ward B to prevent any possible cross-talk between the different interventions.

To ensure the confidentiality of the allocation sequence, an independent team member will be responsible for the randomization process and be neither involved in participant registration nor in intervening in the allocation. This is to prevent disclosure of the sequence during the course of the study. This team member then forward the allocation results to the intervention team. By doing this, both the participant enrollment team and the intervention team know nothing about the allocation in advance.

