Finally, given the uniqueness of the AI-HEALS intervention in this trial, complete blinding of participants and therapists will be infeasible. This limitation may introduce biases such as performance bias due to participants’ awareness of their treatment allocation and detection bias from therapists’ knowledge of the implemented intervention. To minimize these biases, a series of measures will be implemented to reduce bias impact on this study. First, the identities of all intervention and control group participants will remain concealed until study completion. Second, an independent team member not involved in participant enrollment or intervention delivery will oversee the randomization process. This individual will directly forward allocation results to the intervention team to ensure both the enrollment and intervention teams remain unaware of group assignments in advance. Third, intervention group patients will be hospitalized in Ward A while controls occupy Ward B to prevent cross-contamination between groups. Finally, to further mitigate bias, research assistants blinded to group assignments will collect study data. Additionally, data analysts will remain blinded to group allocations during the analysis phase. Data will be coded and kept confidential throughout the study to preserve the integrity of the blinding process.

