Before the study starts, experts will organize training sessions and evaluations to ensure all team members understand the procedures and technical details. To reduce the risk of missing follow-up, we will keep a list of all participants and assign each one a unique identification code. Also, to ensure both the intervention and control groups are consistent, all survey times will be the same, and the same validated questionnaires will be used. To make sure the data is accurate, we will use a double data entry and checking process, which will improve data quality. We will also talk to statistical experts regularly to choose the best methods for the study. During data processing, if we find any abnormal data, we will check the original questionnaires to make sure the data is correct. Only after confirming that the data is fully accurate will we use it for the final analysis.

The principal investigators will regularly check the work of the research team to make sure the study protocol is followed and the data is collected properly. If the team does not follow the survey and follow-up procedures, the investigators may take action, such as stopping the trial or changing the randomization plan. After these changes, data collection will start again. If there are problems with the questionnaire design or mistakes in recording data, the team will stop the trial, fix the issues, and redesign the questionnaire. After making the changes, the updated questionnaire will be given to participants to ensure the data matches the study’s goals and expected results. This will help keep the study’s science and data reliable, ensuring the results are valid. The data will be managed by a data administrator. The trial manager will oversee data recording and handle any problems with cloud storage, data management, and access. The trial manager will also check regularly to ensure the data is accurate, reliable, and follows the study protocol.

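### Study management lets the investigators change the randomization plan after procedural lapses and start data collection again, which does not fit the trigger and puts the predefined, independently run allocation at risk

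*Protocol article*

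**What the plan says.** Section 3 (Study management) has the principal investigators check the team's work regularly. If survey and follow-up procedures are not followed, "the investigators may take action, such as stopping the trial or changing the randomization plan". The next sentence is: "After these changes, data collection will start again".

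Section 2.2 (Randomization and blinding) describes the allocation differently. Numbers are computer-generated, the ratio is 1:1, and "each patient is assigned to the appropriate study group in a predefined order". Control of the process lies outside the investigators: "an independent team member will be responsible for the randomization process and be neither involved in participant registration nor in intervening in the allocation". On blinding, "research assistants blinded to group assignments will collect study data" and "data analysts will remain blinded to group allocations during the analysis phase". The section does not blind the principal investigators, and the two arms are placed in different wards.

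Other parts of the article bear on the point:

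- Section 2.12 (Statistical analysis) promises an intention-to-treat analysis and two-sided tests at 0.05.
- Section 2.9.2 (Secondary outcomes) collects the recruitment rate, the dropout rate and the reasons for withdrawal.
- Section 3 sends every proposed change to the steering committee, then to the ethics committee and the research department. It also gives the data monitoring committee power to suspend or terminate the study for deviations or unauthorised changes.
- Section 3 has two related clauses. One allows the study to be redesigned and restarted after a serious fault in the AI system. The other allows the trial to be stopped and the questionnaire redesigned.

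**The concern.** The remedy does not match the problem. Missed surveys and poor follow-up happen after allocation, so a different allocation plan does nothing to correct them. An allocation plan that can be altered because of how the trial is running is also no longer predefined in the sense of section 2.2. The power to alter it is given to the investigators, whereas section 2.2 keeps randomization with an independent person.

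Three things are left open: who would generate and hold a revised sequence, whether the decision would be taken without sight of data by arm, and what becomes of children already randomised. If they were set aside, the analysis would no longer include everyone randomised. The recruitment and dropout rates would then describe only the later start. That matters in a pilot, because poor follow-up is one of the operational problems it should record.

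**Working it through.** The article gives no figure on this point. The check is a comparison of the sections, followed by an illustration of when a restart does statistical harm.

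**Comparison of the sections**

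| Question | Section 2.2 | Section 3 |
|---|---|---|
| Is the allocation plan fixed in advance? | Yes, predefined order | May be changed mid-trial |
| Who controls it? | Independent team member | Investigators may act; changes go to committees |
| What triggers a change? | None foreseen | Lapses in survey and follow-up procedures |
| What happens to children already randomised? | Not addressed | Not addressed |
| Must the decision be blind to data by arm? | Collectors and analysts are blinded; investigators not mentioned | No such requirement |

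**Effect on the error rate**

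Inputs: 25 evaluable children per arm (section 2.4) and two-sided 0.05 (section 2.12). Assumptions: no true effect, normal outcomes, a t-test, and a restart that discards the first start and enrols a full new one. The article does not state that last assumption; it is the worst reading.

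1. *Restart unrelated to the data.* The reported start is a single valid trial. Two-sided error is 0.05, of which 0.025 favours the intervention. Simulation with a random half of trials restarted: 0.050 and 0.025.
2. *Restart because the half-way trend is unfavourable.* By symmetry the two-sided error stays at 0.05. Half of the trials are restarted, and these contribute 0.5 × 0.025 = 0.0125 in favour of the intervention. The half that continue contribute slightly less than 0.025. The sum is just under 0.0375 against a nominal 0.025. Simulation (12 per arm at the look): about 0.05 two-sided, and 0.036 to 0.037 in favour of the intervention.
3. *Restart because a completed start is not significant.* If either of two independent full starts can become the reported one, the error is 1 − 0.95² = 1 − 0.9025 = 0.0975. Simulation: about 0.097 two-sided, and 0.048 to 0.049 in favour of the intervention.

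**Effect on the counts**

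The article does not say when a restart might occur, so the number already enrolled is an assumption. Against the planned 60, setting aside 10, 20 or 30 children would remove 10/60 = 17%, 20/60 = 33% or 30/60 = 50% of planned enrolment from the recruitment and dropout figures.

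**The case against.** The strongest case against the point is that the safeguards are real. Every change passes the steering committee, the ethics committee and the research department, is documented, and leads to an updated trial application. The monitoring committee can halt the study over unauthorised changes. The trigger is staff conduct, not results. No comparative interim look is described. The real-time records in section 2.7.2 are diary entries from families using AI-HEALS, not C-ACT scores by arm. Section 2.4 says the pilot is not designed for hypothesis testing.

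Much of this stands, and it makes a unilateral or results-driven change less likely. It does not close the gap. Approval settles who agrees to a change. It does not ensure that the decision is made without data by arm, that randomised children are retained, or that an abandoned start is reported. An approved change would not count as unauthorised. Despite section 2.4, section 2.12 still plans tests at 0.05, and the Discussion makes improved asthma control the main purpose.

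A reader might go further and infer that the clause breaks concealment and the intention-to-treat set, or that the trial's false-positive rate is 9.75%. The article supports neither reading. A revised sequence could be concealed as well as the first, and nothing removes the independent team member's role. Starting data collection again may mean resuming after a pause, and nothing says that earlier children or their data are dropped. The 9.75% needs a completed, tested, non-significant start to be replaced, which is not what a clause about procedural lapses describes.

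**Conclusion.** The point holds in a limited form. Section 3 states a rule that cannot remedy its own trigger and conflicts with the predefined, independently run allocation in section 2.2. The oversight in section 3 reduces the risk but does not remove it. Concealment, the intention-to-treat set and the feasibility rates are exposed, not necessarily lost.

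The size depends on how a restart would be used. With a restart unrelated to the data there is no inflation. With a restart prompted by an unfavourable half-way trend, the chance of a false result in favour of the intervention is about 0.037 instead of 0.025. The upper bound is 0.0975 two-sided if a completed non-significant start is replaced. These figures assume no true effect, 25 per arm and full replacement of the first start. Because the text does not exclude a data-aware restart and the correction is small, the clause should be changed.

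**What to change.** In section 3:

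- Delete the option to change the randomization plan when procedures are not followed.
- Replace the sentence on starting data collection again with a statement that it resumes under the same allocation list.
- State that procedural lapses are handled by retraining and logged as deviations.
- State that every randomised child stays in the analysis and in the recruitment and dropout counts.
- Apply the same retention and reporting rule to the clause on redesigning and restarting after an AI system fault and to the clause on questionnaire redesign. Otherwise the same gap remains there.

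The cost is a few lines of wording, approved through the amendment route that section 3 already describes. The one real loss is the option to re-randomise after a procedural failure.

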#### Primary outcomes

2.9.1

The primary outcome was changes in asthma symptom control, measured using the Childhood Asthma Control Test (C-ACT) at baseline, discharge, and post-intervention. Given the nested longitudinal structure of repeated measurements within families, we employed multilevel negative binomial models to analyze asthma symptom frequency (count data), estimating incidence rate ratios (IRRs) and 95% confidence intervals (CIs).

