### Questionnaires

2.11

Childhood Asthma Control Test (C-ACT): The C-ACT is an important tool for measuring how well asthma symptoms are controlled in children. It has two parts with a total of seven questions in Chinese version. The first part has four questions for the child to answer. Each question is scored from 0 to 3, based on how the child feels about their asthma control. The second part has three questions for the parent to answer. Each question is scored from 0 to 5, based on how often the child has asthma symptoms in the last four weeks. The total score of the C-ACT goes from 0 to 27. A score of 23 or higher means asthma is fully controlled, with few symptoms affecting daily life. A score between 20 and 22 means partial control, where symptoms are somewhat managed, but some problems remain. A score of 19 or less means asthma is not controlled, and stronger treatments may be needed (31).Short-Form Egna Minnen av Barndoms Uppfostran for Chinese (s-EMBU-C): The s-EMBU-C is a questionnaire designed to evaluate how children see their parents’ parenting styles. The child fills out this questionnaire. There are separate versions for fathers and mothers. Each version has 21 questions, divided into three parts: rejection (6 items), emotional warmth (7 items), and overprotection (8 items). The questions are scored using a scale from 1 to 4. “Never” gets 1 point, “Occasionally” gets 2 points, “Frequently” gets 3 points, and “Always” gets 4 points. Item 15 is scored in reverse. The scores for each part are found by adding up the points for each question in that part. A higher score in a part means the parent shows that parenting style more often. The total score for both versions can range from 28 to 112 points (32).The assessment of depression and anxiety will use the Chinese version of the Patient Health Questionnaire-4 (PHQ-4). This is a short self-report tool to check depression and anxiety symptoms over the past two weeks. The PHQ-4 has four questions. The first two questions focus on depression symptoms, and the last two focus on anxiety symptoms. Each question is rated on a scale from 0 to 3: “Not at all” (0 points), “Several days” (1 point), “More than half the days” (2 points), and “Nearly every day” (3 points). The total score goes from 0 to 12. In studies in China, the PHQ-4 has shown high validity and reliability, with a Cronbach’s alpha of 0.833 (33).The Chinese version of the Perceived Social Support Scale-Short Form (PSSS-SF) is used to measure the level of social support a person feels they receive. The scale has three questions, each about a different type of support: family support (Item 1), friend support (Item 2), and other support (Item 3). Each question is scored on a 7-point scale from 1 (Strongly Disagree) to 7 (Strongly Agree). The total score can range from 3 to 21. Higher scores mean more social support, showing that the person’s social network provides more help, both emotionally and practically (34).The Chinese version of the New General Self-Efficacy Scale (NGSES-SF) is used to measure a person’s confidence in their ability to succeed in tasks or face challenges. It has three questions, each focusing on a different aspect of self-efficacy. Item 1 looks at how capable a person feels in handling a situation. Item 2 focuses on how confident a person is in their skills. Item 3 looks at how confidence in one area can apply to other areas. The NGSES-SF uses a 5-point Likert scale. Respondents can choose from 1 (Strongly Disagree), showing low confidence, to 5 (Strongly Agree), showing high confidence. The total score can range from 3 to 15 (35).The Chinese version of the EQ-5D-5L scale (EuroQol-5 Dimensions 5 Levels) will be used to measure quality of life. The scale looks at five important health areas: mobility, self-care, usual activities, pain/discomfort, and anxiety/depression. For each area, there are five levels, ranging from “no problems” to “extreme problems.” This lets respondents choose the level that best matches their condition. It gives a complete view of a person’s health in these five areas. The EQ-5D-5L also includes a Visual Analogue Scale (VAS). This part lets participants rate how they feel about their current health on a scale from 0 to 100. A score closer to 0 means worse health, while a score closer to 100 shows better health (36).Smoking behavior will be assessed using a self-designed questionnaire. The questionnaire has four multiple-choice questions to categorize smoking habits. These questions are meant to find out: whether the person smokes, how long it has been since they quit smoking (if they quit), how many cigarettes they smoke daily, and when they started smoking. The first question is “Do you have a smoking habit?” with these options: (1) Yes, I smoke regular cigarettes; (2) Yes, I smoke e-cigarettes; (3) I smoke both; (4) I used to smoke (now quit); (5) I have never smoked. Based on their answers, participants will be grouped into two categories: smokers, which include people who currently smoke regular cigarettes, e-cigarettes, or both; and non-smokers, which include those who have never smoked and those who have quit smoking (37).Alcohol consumption will be evaluated using a self-developed 7-item multiple-choice questionnaire designed to assess: 1) current/historical alcohol use status, 2) age of drinking initiation, 3) age of drinking cessation (if applicable), 4) preferred alcoholic beverage types, 5) average daily alcohol intake, 6) pre-quitting daily consumption volume, and 7) perceived anxiety related to alcohol cessation. The instrument begins with the core screening question: ‘Which best describes your alcohol consumption pattern?’ Respondents choose from four mutually exclusive categories: (1) Never consumed alcohol; (2) Current regular drinker; (3) Former drinker who has quit; (4) New-onset drinker in the past year (43, 44).The Chinese version of the Pittsburgh Sleep Quality Index Short Form (PSQI-SF) is a shorter version of the Pittsburgh Sleep Quality Index, made to measure sleep quality. The scale has six items, covering five key aspects of sleep. Items 1 and 2 measure sleep efficiency. Item 3 measures how long it takes to fall asleep. Item 4 looks at sleep duration. Item 5 checks for sleep disturbances. Item 6 looks at overall sleep quality. The total score on the PSQI-SF goes from 0 to 15. A higher score means worse sleep quality (38).The Chinese version of the Family Communication Scale Short Form (FCS-SF) is made to measure how well family members communicate. The scale has four items that assess family communication. It uses a 5-point Likert scale, where 1 means “strongly disagree” and 5 means “strongly agree.” The total score goes from 4 to 20. A higher score means better communication among family members (39).The Chinese version of the Electronic Health Literacy Scale (eHEALS) measures how well parents of children can search for, evaluate, and use electronic health information to solve health problems. The scale has five items in one dimension. It uses a 5-point Likert scale, where 1 means “strongly disagree” and 5 means “strongly agree.” The total score ranges from 5 to 25. A higher score means better electronic health literacy (40).

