This study allowed unblinding in special situations. These situations include urgent medical needs, such as when a participant has a serious adverse event or needs urgent treatment where knowing the group assignment is important. Unblinding can also happen for valid medical reasons by the participant or their healthcare provider after the study ends. The unblinding process starts with a written request from the principal investigator or a member of the clinical oversight team. The Clinical Review Panel will review all unblinding requests to decide if the conditions are met. If approved, the study team will securely reveal the group assignments following a set protocol.

All proposed changes to the study will first be discussed by the steering committee. After agreeing, the changes will be sent to the hospital’s ethics committee and the research department for approval. Once approved, an official document with the changes will be given to all relevant parties, and an electronic copy will be available if needed. Any changes from the protocol will be recorded by the trial leader and signed by the principal investigator. This document will be kept with the other trial records. After getting approval from the steering committee, research department, and ethics committee, the trial leader will update the clinical trial application.

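### The rule for redesigning questionnaires mid-trial aims at agreement with expected results, is triggered even by recording mistakes, and does not exempt the primary C-ACT

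*Protocol article*

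**What the plan says.** Study management (section 3 of the protocol article) sets an operative rule. The trigger is: "If there are problems with the questionnaire design or mistakes in recording data". The action is: "the team will stop the trial, fix the issues, and redesign the questionnaire". After that, "the updated questionnaire will be given to participants to ensure the data matches the study’s goals and expected results". No instrument is named and none is exempted.

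The same section says that, for consistency between the two groups, "all survey times will be the same, and the same validated questionnaires will be used". It also says that abnormal values found during data processing are checked against the original questionnaires, and it provides for double data entry.

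On the primary endpoint, section 2.9.1 states: "The primary outcome was changes in asthma symptom control, measured using the Childhood Asthma Control Test (C-ACT) at baseline, discharge, and post-intervention". Section 2.11 (Questionnaires) lists the C-ACT first and describes four child items scored 0 to 3 and three parent items scored 0 to 5. It adds: "The total score of the C-ACT goes from 0 to 27". Scores of 23 or more, 20 to 22, and 19 or less define full, partial and no control.

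On change control, Study management states: "All proposed changes to the study will first be discussed by the steering committee". The ethics committee and the research department must then approve.

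**The concern.** Three features of the rule are wrong as written.

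- **Aim.** An instrument may be corrected because it is ambiguous, misprinted or unanswerable. That the data should come out as expected is not an admissible reason, because it makes the hoped-for finding the standard by which the measure is judged.
- **Trigger.** A mistake in recording is an error in the data. It is cured by going back to source and gives no ground for altering the instrument.
- **Scope.** The rule covers any questionnaire, and the primary outcome is a questionnaire score analysed as change over three time points.

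At stake is the comparability of the C-ACT within a child. If items change between baseline, discharge and 3 months, the change score contains the difference between two versions as well as any change in asthma control. The published cut-offs would no longer apply to the later score.

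**Working it through.** The plan states no figure on this point, so the check is mainly textual, with a little algebra to show where bias could and could not arise.

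**1. Does the rule reach the C-ACT?** The trigger speaks of questionnaire design without restriction. Section 2.11 lists the C-ACT among the questionnaires, beside the self-designed smoking and alcohol forms. Nothing in section 3 separates the two kinds. The C-ACT is therefore not excluded, though it is not named.

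**2. Is the C-ACT score tied to a fixed item set?** From section 2.11: 4 × 3 + 3 × 5 = 12 + 15 = 27, which agrees with the stated maximum. The range and the cut-offs belong to these seven items with this scoring. Removing, adding or rescoring an item changes what 20 or 23 means.

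**3. What would a version change do to the endpoint?** Let a new version shift a child's score by d_I points on average in the intervention arm and d_C in the control arm. Let p_I and p_C be the shares of each arm whose baseline is on the old version and whose 3-month score is on the new one. Then:

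- Shift in mean change: p_I × d_I and p_C × d_C.
- Bias in the difference between arms: p_I × d_I − p_C × d_C.
- If d_I = d_C = d, this is d × (p_I − p_C). If p_I = p_C = p, it is p × (d_I − d_C).
- If both are equal, the bias is zero. What remains is the within-arm shift p × d and added variance of d² × p × (1 − p) in the change score, because some children switch and others do not.

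**4. Is p_I − p_C likely to differ from zero?** Allocation is 1:1 (section 2.2), survey times are the same in both groups, and nothing describes a roll-out by arm. A switch would follow calendar time, so the expected difference is about zero. For chance imbalance, take 30 per arm (section 2.4) and assume a common share p of children who switch, since the documents give none. The standard deviation of p_I − p_C is √(2 × p × (1 − p) / 30):

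- p = 0.1: √(2 × 0.09 / 30) = √0.006 = 0.08.
- p = 0.5: √(2 × 0.25 / 30) = √0.0167 = 0.13.

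So a one-standard-deviation imbalance would move the difference between arms by about 0.08 to 0.13 points per point of version shift d. This is chance error, which averages out over repetitions. The documents give nothing from which to set d, so no bias in C-ACT points can be derived.

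**5. Could d_I and d_C differ?** They could if the new items happened to favour one arm, for example by asking about something that the intervention teaches. The documents neither indicate this nor exclude it.

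**6. What does existing change control cover?** Approval by the steering committee, ethics committee and research department settles who agrees to a change. It does not keep the primary instrument fixed, require the decision to be taken without sight of outcome data by arm, or say what happens to data from the previous version.

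**The case against.** The strongest reply is that the phrase is loosely worded and that the rule is ordinary fault repair. Much of that stands.

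- A reader might infer that the protocol plans to alter instruments when results disappoint. It does not say so. The trigger is a design fault or a recording mistake, and the following sentence gives reliable data as the purpose. The reference to expected results may simply mean intended purpose.
- A reader might infer that a C-ACT redesign is planned. It is not. Design faults fit the self-made forms more naturally, and the C-ACT is reached only because the wording is unrestricted.
- A reader might see a flat contradiction with the statement that "the same validated questionnaires will be used". In context that is a promise of parity between arms, and an updated form given to everyone would keep it. The word validated still sits badly with redesign by the study team, but the text does not clearly promise sameness over time.
- A reader might infer that changes would be made with sight of outcome data by arm. This is not documented. Data collectors and analysts are blinded (section 2.2), the real-time backend view in section 2.7.2 covers lifestyle records and does not list the C-ACT, and no interim comparison is described. The investigators who would do the redesign are not stated to be blinded, so the risk is not excluded.
- Approval of changes is already required, and the data monitoring committee may suspend the study for unauthorised ones.
- This is a pilot, meant among other things to expose operational problems (section 2.4). That tempers the stakes, although sections 2.9.1 and 2.12 still plan effect estimates and tests.

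None of this makes expected results a proper aim, or a recording mistake a reason to change a scale.

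**Conclusion.** The point holds as a defect in a stated rule, and a fuller protocol or analysis plan would not cure the wording. Followed literally, the rule permits mid-trial changes to any scored instrument, for an improper aim and on a trigger that does not call for one. For the C-ACT, the consequence would mainly be a version effect and added noise in within-child change. Bias between arms needs version use or version effect to differ by arm. In expectation the former is about zero, and nothing in the documents indicates the latter. No size in C-ACT points can be derived. The conclusion assumes only that the rule means what it says and that its unrestricted wording includes the C-ACT. If the authors meant something narrower, the correction costs even less.

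**What to change.** Amend Study management as follows.

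1. Strike the reference to expected results.
2. State that the C-ACT and the other validated scales stay unchanged from first enrolment to last assessment.
3. Separate the two triggers. Recording mistakes are corrected against the original questionnaire, as the section already provides for abnormal data.
4. Limit any redesign to self-developed forms. Such changes are decided without sight of outcome data by arm and approved through the existing change-control route. The version and date are recorded for each assessment, and data collected on the previous form are retained.

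The cost is a short wording change. It needs no additional visits or participants. The only new task is to log the form version where a self-developed form is changed.
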